### Study endpoints

The primary outcome variables are PPC and PCT kinetics. PPC are defined as new infiltrates or atelectasis on a chest X-ray, abnormal breathing sounds on auscultation, respiratory failure defined as PaO_2_/FiO_2_ < 300 or the need for noninvasive or invasive ventilatory support within the first three postoperative days. PCT kinetics will be evaluated during and after surgery. Blood samples will be taken at 0, 2, 6, 12, 24, 48 and 72 h after surgical incision. According to recent data it is expected that PCT values will peak at approximately 24 h after surgery and that they should decline by approximately 50% daily in the case of an uneventful postoperative course. Therefore, in addition to the absolute values the change between T_0_–T_24_–T_48_ will also be evaluated [16, 22].

Secondary outcome variables are extrapulmonary complications: incidence of circulatory failure, gastrointestinal and renal dysfunction, hematologic and coagulation disorders and infection (Table 1).

**Table 1 Tab1:** Secondary endpoints

Endpoint	Time frame	Detailed description
Circulatory failure	28 days	Hypotension – MAP < 65 mmHg
		Severe cardiac arrhythmia – 40/min < HR > 150/min
		ScvO_2_ < 70%
		dCO_2_ > 7 mmHg
		Serum lactate > 2 mmol/L
		Severe metabolic acidosis (actual bicarbonate < 18 mmol/L)
		Acute coronary syndrome
		Acute left ventricular failure
		Pulmonary embolism
		Cardiac arrest
Gastrointestinal dysfunction	28 days	Constipation
		Ileus
		Anastomotic leakage
		Reoperation
		Disorders of liver function
Renal dysfunction	28 days	RIFLE criteria
Hematologic and coagulation disorders	28 days	Severe bleeding
		Coagulopathy – INR > 1.5
Infection	28 days	Any infection except from pneumonia

*MAP* mean arterial pressure, *HR* heart rate, *ScvO*
_*2*_ central venous oxygen saturation, *dCO*
_*2*_ central venous-to-arterial carbon dioxide gap, *INR* International Normalized Ratio

Tertiary endpoints are intensive care unit (ICU) days, in-hospital stay, in-hospital and 28-day mortality.

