### Study arms and assigned intraoperative interventions

A total number of 40 patients with bladder cancer submitted to general anesthesia and open radical cystectomy and urinary diversion will be enrolled in this study. An equal number of patients will be randomized into the two groups.

Patients randomized into the SG group undergo an alveolar recruitment maneuver using the sustained airway pressure by the CPAP method, applying 30 cmH_2_O PEEP for 30 s followed by a decremental PEEP titration procedure directed by Cstat. During the PEEP titration procedure, PEEP will be decreased from 14 cmH_2_O by 2 cmH_2_O every 4 min, until a final PEEP of 6 cmH_2_O is reached. On each level of PEEP, ABGs will be collected and evaluated. Optimal PEEP is considered as the PEEP value resulting the highest possible Cstat measured by the ventilator. After the PEEP titration procedure, lung-protective mechanical ventilation will be performed using optimal PEEP and low tidal volumes and ARM will be performed every 60 min.

Patients randomized into the CG group will undergo an alveolar recruitment maneuver using the sustained airway pressure by the CPAP method, applying 30 cmH_2_O PEEP for 30 s followed by low-tidal-volume LPV using a PEEP value of 6 cmH_2_O and ARM will be repeated every 60 min.

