### Statistics

Data will be analyzed by the research team in collaboration with a medically versed biostatistician after completion of the trial. There will be no interim analysis. Statistical analysis will be conducted on an intention-to-treat basis. IBM SPSS 20.0 statistical software will be used for analysis.

It is expected that the majority of source data will be recorded onto CRF; nonetheless, before starting the data analysis, the mechanism and pattern of missing data will be evaluated and these findings will be used to determine whether they have had an impact on the statistical analysis and results and how they can be managed.

Data distribution will be tested by the Kolmogorov-Smirnov analysis. Normally distributed data will be presented as mean and standard deviation (SD) and skewed data as median (interquartile range). Comparing related samples, the paired and unpaired *t* test will be used for normally distributed data and the Wilcoxon signed rank test and Mann-Whitney *U* test for skewed data. Differences in proportions will be evaluated using the Fisher’s exact test, and risk ratio with associated 95% confidence interval (CI). Analysis of the primary endpoint (PPC) will be carried out by the unpaired Student’s *t* test (95% CI). A two-way, repeated-measures analysis of variance (two-way RM ANOVA) will be used to compare the groups’ serum PCT levels. The relationship between PCT levels and organ dysfunctions will be evaluated using the Pearson correlation. Statistical analysis of SOFA scores, ICU days, in-hospital stay, in-hospital and 28-day mortality data of groups will be implemented by the chi-square test. A *P* value < 0.05 will be considered significant.

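### Chi-square is fixed for SOFA scores, ICU days and hospital stay without any grouping: it ignores order, loses much power at 20 per arm, and conflicts with the plan's own Mann-Whitney and Fisher rules

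*Protocol article*

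**What the plan says.** The Statistics section puts five measures under one test: "Statistical analysis of SOFA scores, ICU days, in-hospital stay, in-hospital and 28-day mortality data of groups will be implemented by the chi-square test". Their scales differ:

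- **ICU days, hospital stay, mortality.** Study endpoints gives their rank: "Tertiary endpoints are intensive care unit (ICU) days, in-hospital stay, in-hospital and 28-day mortality". The first two are counts of days; the two mortality endpoints are yes/no.
- **SOFA.** This is an ordinal score. The Postoperative care section has it recorded daily to follow the secondary endpoints, and the Abstract names SOFA-monitored organ dysfunction among the secondary and tertiary endpoints.

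The same paragraph of the Statistics section also sets general rules:

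- "the paired and unpaired *t* test will be used for normally distributed data"
- "the Wilcoxon signed rank test and Mann-Whitney *U* test for skewed data"
- "Differences in proportions will be evaluated using the Fisher’s exact test", with a risk ratio and 95% confidence interval
- "A *P* value < 0.05 will be considered significant"

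No threshold, grouping or summary is given that would turn SOFA, ICU days or hospital stay into categories.

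**The concern.** Pearson's chi-square compares two groups across unordered categories. Its statistic does not change when the category labels are permuted, so a difference between 8 and 9 days counts the same as a difference between 8 and 40. Two counts of days and an ordinal score carry their information in exactly the ordering that the test discards.

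The sentence also departs from the rules just before it without giving a reason. For SOFA and the stays it displaces the t test or Mann-Whitney; for mortality it displaces Fisher's exact test. An analyst who reads the whole paragraph has two named tests for each of these endpoints. If the choice is made after the data are seen, the reported P value can depend on it.

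The hypothesis in the Background includes less organ dysfunction, better survival and shorter stay. A real difference in SOFA or stay could be reported as absent because of the test rather than the data.

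**Working it through.** **Inputs from the protocol article.** Total N = 40 (Study arms and assigned intraoperative interventions); 1:1 allocation in 10 blocks of four (Blinding, data collection, randomization and record-keeping), so 10 × 4 = 40 and 20 per arm. Significance threshold 0.05, taken here as two-sided. The article gives no effect size, SD, event rate or power, so there is no stated power figure to reproduce.

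**Step 1. A result that needs no distributional assumption.** Suppose all 40 hospital stays differ. Each value then forms a column with one patient, and the expected count is 0.5 in each arm. The column contributes (1 − 0.5)²/0.5 + (0 − 0.5)²/0.5 = 1. Over 40 columns the statistic is 40 on 39 degrees of freedom, P = 0.43, whatever the data are. If every patient in one arm leaves before every patient in the other, chi-square still gives 0.43; Mann-Whitney gives 6.8 × 10⁻⁸.

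The converse also occurs. With five distinct values per arm, four patients each, and none shared between arms, chi-square gives P = 7.6 × 10⁻⁶ whether the second arm lies wholly above, wholly below or on both sides of the first. Mann-Whitney gives 5.9 × 10⁻⁸, 5.9 × 10⁻⁸ and 0.28.

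**Step 2. Power under assumed distributions.** Simulation, 20 per arm, 3000 runs per row (Monte Carlo standard error at most √(0.25/3000) = 0.9 points). Stays are log-normal rounded to whole days; SOFA is Poisson. With k distinct values the mean expected count per cell is 40/(2k).

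| Endpoint (assumed) | Mean expected count | Chi-square | Mann-Whitney |
|---|---|---|---|
| Hospital stay, median 14 v 10, log-SD 0.4 | 1.2 | 4% | 71% |
| ICU days, median 3 v 2, log-SD 0.5 | 3.0 | 25% | 66% |
| SOFA, mean 3 v 1.8 | 2.8 | 22% | 64% |

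With no true difference, chi-square rejected in 0.4–1.0% of runs for hospital stay and about 2–3% for ICU days and SOFA, against a nominal 5%.

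**Step 3. Sensitivity to the assumptions.**

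- Hospital stay 14 v 10 with log-SD 0.3 / 0.4 / 0.5: chi-square 15% / 4% / 1%, Mann-Whitney 91% / 71% / 52%.
- ICU days 4 v 2.5: 26% against 80%. ICU days 4 v 3: 9% against 38%.
- SOFA as a rounded normal with SD 2: 4 v 2, 37% against 84%; 4 v 2.4, 21% against 66%; 4 v 3, 8% against 31%.

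**Step 4. Mortality.** Take 0/20 v 4/20 deaths. Expected deaths are 2 per arm and expected survivors 18 per arm. The uncorrected statistic is 2 × (2²/2) + 2 × (2²/18) = 4.44, P = 0.035. With continuity correction it is 1.5² × (2/2 + 2/18) = 2.5, P = 0.114. Fisher's exact P = 0.106. At the 0.05 threshold, uncorrected chi-square and Fisher reach opposite conclusions on this table.

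**The case against.** **The sentence may presuppose grouping.** If the values were split at the pooled median, chi-square would keep more power: 34–76% for hospital stay (14 v 10), 48–62% for ICU days (3 v 2; 4 v 2.5) and 48–66% for SOFA (4 v 2.4; 4 v 2). This is fair, and it limits any claim about size. But the article names the test and states no split, and even the median split stays below Mann-Whitney in the same scenarios.

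**A specific rule overrides a general one.** The sentence could be read as a deliberate exception to the t test/Mann-Whitney and Fisher rules. Nothing in the section says so or gives a reason, and an exception would still leave an order-blind test on ordered data.

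**Low power is partly the sample size.** A t test with 20 per arm has about 35% power at a standardised difference of 0.5 and 72% at 0.8. At the smaller effects in step 3, Mann-Whitney itself reaches only 31–38%. This stands; the test choice adds a further loss.

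**Stronger readings that a reader might infer.**

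- *Almost no power for all three measures.* This fits hospital stay only, with its many distinct values. In the step 2 scenarios ICU days and SOFA keep roughly a third of the Mann-Whitney power, and expected counts near 1 likewise apply to hospital stay alone.
- *Chi-square will produce false-positive mortality findings.* The exact type I error of the uncorrected test at 20 per arm is 0.3%, 1.2%, 3.9% and 5.0% at assumed mortality of 3%, 5%, 10% and 20%: conservative or nominal. The article does not say whether the corrected version is meant, and that version agrees with Fisher on the table in step 4.
- *The correlation sentence has the same fault:* "The relationship between PCT levels and organ dysfunctions will be evaluated using the Pearson correlation". Pearson's coefficient against a yes/no variable is the valid point-biserial correlation. Organ dysfunction need not be yes/no either, since the Abstract ties it to SOFA and Table 1 gives only the RIFLE criteria for the kidney. An illustrative comparison gave 66% power for Pearson and 72% for Spearman, too small a loss to raise.

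**Conclusion.** The plan is wrong as written for SOFA scores, ICU days and hospital stay. The loss of order and magnitude, and the conflict with the t test/Mann-Whitney rule, follow from the text and from the test itself, whatever the data look like. The size of the power loss rests on assumed distributions, because the article supplies none. In the main scenarios power drops from about 70% to about 4% for hospital stay, and from about 65% to about 24% for ICU days and SOFA.

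For in-hospital and 28-day mortality the finding is narrower. Two tests are named for the same kind of data and they can disagree at 0.05. Chi-square is not generally inflated there.

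This should be fixed, but it is not critical. ICU days, stay and mortality are tertiary, SOFA serves the secondary endpoints, and the primary endpoints do not depend on this sentence.

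**What to change.** Replace the chi-square sentence with wording to this effect:

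- ICU days, hospital stay and one prespecified SOFA summary (for example the maximum or the mean over stated days) will be compared by the Mann-Whitney U test, with an estimate of the difference and its 95% confidence interval.
- A stated rule covers patients who die in hospital, since death shortens a stay without being a good outcome. One option is to rank deaths as the worst result; another is to analyse time to discharge with death handled explicitly.
- In-hospital and 28-day mortality will be compared by Fisher's exact test, with the risk ratio and 95% confidence interval that the section already specifies for proportions.

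If a categorical comparison is really intended for any of the three measures, state the cut-off and its reason before the data are analysed.

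The cost is one reworded sentence and two decisions, on the SOFA summary and the handling of deaths. Mann-Whitney and Fisher are already named in the section, and no new data or patients are needed.

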### Adverse events and interruption of the trial

Every patient included in the trial will receive daily visits from an intensive care therapist and urologist in charge from POD 1 until leaving the hospital. During ICU stay, and if necessary on the intermediate care unit, all patients will be continuously monitored. The study nurse will be responsible for collecting blood samples and will record relevant required data onto CRF. During the out-of-hospital follow-up period (until POD 28) patients’ progress, particularly deterioration will be checked by daily phone-call visits.

The investigators will monitor the patients for any adverse events (AEs), which are defined as severe or prolonged hypotension (systolic blood pressure < 90 mmHg) and significant cardiac arrhythmias associated with the PEEP titration procedure. AEs will be documented on the CRF and the principal investigator will be informed.

Serious adverse events (SAEs) are defined as severe barotrauma leading to pneumothorax, significant prolongation of hospitalization, persistent or significant disability or incapacity, and severe deterioration (life-threatening state or even death) associated with the PEEP titration procedure. All treatment-related SAEs will be recorded and reported to the Hungarian Scientific and Medical Research Council Ethics Committee and the Local Ethics Committees. If any SAEs occur, the trial will be interrupted and an investigation will be performed.

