**Discussion:**

This trial will assess the possible benefits or disadvantages of an individualized lung-protective mechanical ventilation strategy during open radical cystectomy and urinary diversion regarding postoperative pulmonary complications and the inflammatory response.

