#### Intraoperative care

Before induction of anesthesia an epidural catheter and an arterial cannula will be inserted for invasive arterial blood pressure monitoring and blood gas sampling.

Immediately after induction of anesthesia and orotracheal intubation, once a steady state has been reached (Table 2), all patients will be submitted to an ARM using the sustained airway pressure by the CPAP method, applying 30 cmH_2_O PEEP for 30 s. After ARM, PEEP will be set to 6 cmH_2_O in the CG (“standard PEEP”) and LPV (TV = 6 mL/Kg IBW, FiO_2_ = 0.5) will be performed. In the SG (“optimal PEEP”) PEEP will be determined during a Cstat-directed decremental PEEP titration procedure. During surgery ARM will be repeated and arterial and central venous blood gas samples (ABGs, CVBGs) will be evaluated every 60 min. In case of decreased oxygen saturation (SpO_2_ < 94%) rescue ARM will be performed using a FiO_2_ of 1.0. PCT levels will be measured 2, 6, 12, 24, 48 and 72 h after surgical incision.

**Table 2 Tab2:** Steady state after induction of anesthesia

	Parameter	Value
Hemodynamics	Mean arterial pressure	65 mmHg < MAP < 90 mmHg
	Heart rate	50/min < HR < 100/min
Ventilation	SpO_2_	≥96%
	EtCO_2_	35–40 mmHg
Anesthetics	EtSevo	1.0 MAC

*MAP* mean arterial pressure, *HR* heart rate, *SpO*
_*2*_ peripheral capillary oxygen saturation, *EtCO*
_*2*_ end-tidal carbon dioxide partial pressure, *EtSevo* end-tidal sevoflurane concentration, *MAC* minimal alveolar concentration

Arterial blood pressure, heart rate (HR) and end-tidal carbon dioxide tension (EtCO_2_) will be monitored continuously. Cstat, airway resistance (Raw), Vds/Vt, core temperature and train-of-four relaxometry data will be recorded every 15 min.

During surgery, in cases of hypotension, intravenous norepinephrine will be started to maintain mean arterial pressure above 65 mmHg. For intraoperative fluid management patients will receive 3 mL/Kg/h of balanced crystalloid solution until end of surgery. In cases of bleeding, a 200-mL colloid (hydroxyethyl starch, HES) solution bolus and crystalloid substitution will be given. Packed red blood cell (PRBC) transfusion will be given whenever the attending anesthetist feels it necessary.

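### Adverse events are defined by association with a PEEP titration that only the study group undergoes, so AE/SAE counts cannot be compared between arms and barotrauma has no arm-neutral count

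*Protocol article*

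**What the plan says.** All references are to the Protocol article.

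- **AE definition** (Adverse events and interruption of the trial): "severe or prolonged hypotension (systolic blood pressure < 90 mmHg) and significant cardiac arrhythmias associated with the PEEP titration procedure".
- **SAE definition** (same section): barotrauma with pneumothorax, prolonged hospitalization, lasting disability, and finally "severe deterioration (life-threatening state or even death) associated with the PEEP titration procedure".
- **SAE handling** (same section): "All treatment-related SAEs will be recorded and reported to the Hungarian Scientific and Medical Research Council Ethics Committee" and the local committees. Any SAE interrupts the trial for an investigation.
- **Study group** (Study arms and assigned intraoperative interventions): the recruitment maneuver is "followed by a decremental PEEP titration procedure directed by Cstat".
- **Control group** (same section): the maneuver is "followed by low-tidal-volume LPV using a PEEP value of 6 cmH_2_O and ARM will be repeated every 60 min".
- **Both groups** (Intraoperative care): "all patients will be submitted to an ARM using the sustained airway pressure by the CPAP method" after induction, with repeats every 60 minutes.
- **Endpoints** (Study endpoints, Table 1): hypotension (MAP below 65 mmHg) and severe arrhythmia appear under circulatory failure over 28 days. ICU days, hospital stay and mortality are tertiary. None is restricted to one arm.

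**The concern.** A safety count is informative in a randomized trial when the same event, in the same window, can be counted in either arm. Here the qualifying condition is a procedure that belongs to one arm. Read naturally, the rule gives a study-group count and a structural zero for controls.

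Two wrong conclusions could follow. Events in the study group could look like excess harm when the same events in controls had no place to be recorded. Alternatively, the control zero could be read as observed safety. For pneumothorax the problem is sharper, because the SAE list is the only place where the article names it as an outcome.

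**Working it through.** The protocol gives no AE rate and no figure to reproduce. The check is mainly of the text, with a short illustration.

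**Step 1: who can have an event.**

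| | Study group | Control group |
|---|---|---|
| Recruitment maneuver at start and every 60 min | yes | yes |
| PEEP titration | yes | no |
| Event can be associated with titration | yes | no |

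With 40 patients randomized 1:1, each arm has 20. On the natural reading the control count is 0/20 by construction. The recruitment maneuver could cause harm in either arm, but the definitions do not mention it.

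**Step 2: what the endpoints cover instead.**

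| Event in the AE/SAE lists | Arm-neutral counterpart in Study endpoints | Gap |
|---|---|---|
| Hypotension, systolic < 90 mmHg | MAP < 65 mmHg | Different criterion; Table 1 does not say whether intraoperative episodes count |
| Significant arrhythmia | Severe arrhythmia | As printed, the heart-rate criterion (above 40 and above 150) captures only rates above 150 |
| Prolonged hospitalization | In-hospital stay, ICU days | None of substance |
| Death | In-hospital and 28-day mortality | None of substance |
| Barotrauma with pneumothorax | None | Absent from the pulmonary complication definition and from Table 1 |

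A pneumothorax could reach the pulmonary endpoint indirectly, through low PaO2/FiO2, breath sounds or ventilatory support. It would not be identified as such.

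**Step 3: what a comparison of these counts would show (illustration; the event rates are assumed).** With controls fixed at 0/20, the two-sided Fisher p-value for x/20 against 0/20 is 2 × C(20,x)/C(40,x):

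- x = 4: 2 × 4,845/91,390 = 0.106
- x = 5: 2 × 15,504/658,008 = 0.047
- x = 6: 2 × 38,760/3,838,380 = 0.020

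Five study-group events are therefore enough for p < 0.05. Suppose the true rate is the same in both arms but only study-group events are counted. The chance of at least 5 in 20 is then P(X ≥ 5), X ~ Binomial(20, p):

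| Assumed true rate in both arms | Chance of p < 0.05, study-group events only |
|---|---|
| 10% | 4.3% |
| 20% | 37.0% |
| 30% | 76.2% |
| 40% | 94.9% |

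With identical counting in both arms, equal true rates of 10% to 50% give p < 0.05 in about 1.2% to 2.5% of trials.

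**Step 4: what an observed zero would mean.** A genuinely observed 0/20 has an exact two-sided 95% upper limit of 1 − 0.025^(1/20) = 16.8%. A zero produced by the definition carries no such information.

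**The case against.** **The qualifier may attach only to the last item of each list.** On that reading, hypotension and barotrauma can count in controls, and only arrhythmia and severe deterioration are tied to titration. The same section says "The investigators will monitor the patients for any adverse events (AEs" without restricting the arm, and its reporting sentence speaks of treatment-related SAEs, which could be wider than titration. The ambiguity is real, so the zero is the natural reading and not a proven one. A safety definition with two readings, one of which excludes an arm, still needs correcting.

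**A reader might infer that the trial cannot compare harm as it promises.** The documents do not support that. The abstract says "This trial will assess the possible benefits or disadvantages of an individualized lung-protective mechanical ventilation strategy", but the sentence goes on to confine this to pulmonary complications and the inflammatory response, and the main Discussion says mainly those. Both are primary outcomes compared between arms. Several further harms are endpoints in both arms (Step 2).

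**A reader might infer that study-group events after the titration are outside the definition**, and might express the titration (5 levels × 4 min = 20 min) as a share of operating time. That treats a statement about relatedness as a time window. The SAE list includes prolonged stay and disability, which cannot fit a 20-minute window, and the article gives no operating time beyond several hours.

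**No between-arm AE test is specified.** This is correct, so the Fisher figures show only what such a comparison would do.

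**Unblinded attribution is inferred.** The article does not say who judges association. It does say that only participants are blinded, so a count that depends on judged relatedness is open to bias.

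**Conclusion.** The point holds in limited form. On the natural reading, the AE and SAE definitions are arm-asymmetric: controls cannot contribute, harm from the shared recruitment maneuvers is not named, and the counts cannot be compared between groups. Hypotension, arrhythmia, length of stay and mortality are partly covered by arm-neutral endpoints, with intraoperative hypotension left unclear. Pneumothorax or barotrauma has no arm-neutral count at all.

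The size is a control count of 0/20 set by wording. This rests on applying the qualifier to every item in each list. If it applies only to the last items, the asymmetry shrinks to those items. No primary, secondary or tertiary comparison is affected.

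**What to change.** 1. Define the events already listed identically in both arms. Record them from intubation through the existing follow-up to POD 28, whatever the presumed cause.
2. Record relatedness to the ventilation strategy as a separate CRF field, so that it no longer decides whether an event is counted.
3. State whether intraoperative hypotension counts toward the Table 1 endpoint.
4. Report counts by arm with the Fisher's exact test already planned for proportions, and add a risk difference with CI. The planned risk ratio is undefined when the control count is zero.
5. Reconcile the sentence that any SAE interrupts the trial with the wider recording definition. Left as it stands, each prolonged stay or death after major surgery, in either arm, could fall under it. How to settle that is for the investigators.

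The cost is a few more AE entries, one CRF field and one reconciled sentence. No new procedure is needed. Arterial pressure and heart rate are monitored continuously during surgery, and a chest X-ray is taken on POD 1 and read by a radiologist outside the study. Patients are visited daily in hospital and telephoned daily after discharge to POD 28. The trial is ongoing, so the change is best made soon, because intraoperative events that were not recorded may be hard to recover. With 20 per arm the counts will be comparable but imprecise for rare events (Step 4).

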### Data monitoring

Data monitoring will be performed centrally for quality control purposes by an external, independent physician, who will not be involved in the study. Monitoring will evaluate the progress of the study and verify the accuracy and completeness of the data recording (CRF, source data, Informed Consent Forms and outcome variables).

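### SAE recording and trial interruption rest on two different event sets, and the unclear reach of the titration qualifier can leave serious events in controls unrecorded as SAEs

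*Protocol article*

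**What the plan says.** The section *Adverse events and interruption of the trial* of the protocol article contains three statements that have to be read together.

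- **Definition.** The SAE list has four items. Three come first, with no qualifier directly after them: barotrauma with pneumothorax, a significantly longer hospital stay, and lasting disability. The fourth closes the list and carries the tie to titration: "severe deterioration (life-threatening state or even death) associated with the PEEP titration procedure".
- **Recording and reporting.** "All treatment-related SAEs will be recorded and reported to the Hungarian Scientific and Medical Research Council Ethics Committee and the Local Ethics Committees".
- **Interruption.** "If any SAEs occur, the trial will be interrupted and an investigation will be performed".

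The same section defines non-serious adverse events as hypotension and arrhythmia linked to titration, and has the investigators watch for them.

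Four other places bear on the point:

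- *Intraoperative care* and *Study arms and assigned intraoperative interventions* give the titration procedure to the study group only. Both arms receive a recruitment maneuver after intubation and again every 60 minutes.
- *Blinding, data collection, randomization and record-keeping* blinds the participant only.
- *Data monitoring* gives an external physician a quality-control role, which includes to "verify the accuracy and completeness of the data recording".
- Table 1 in *Study endpoints* lists surgical events such as "Anastomotic leakage" as secondary endpoints for all patients.

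**The concern.** The set of SAEs that must be recorded and the set that interrupts the trial are worded differently in adjacent sentences, and the definition feeding both is ambiguous. Two sites applying the same text could therefore record and act on different events.

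Two things are at stake. The first is the meaning of an interruption: if it can be caused by a long stay with no link to ventilation, it says little about harm from the intervention. The second is the safety comparison. If an event counts as an SAE only when it is attributed to a procedure that one arm alone undergoes, the control arm's SAE count is zero by definition. The trial then cannot show whether serious events were more or less frequent with individualized PEEP. As no interim analysis is planned, this section holds the only safety trigger that the article states.

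**Working it through.** The protocol gives no SAE rate and no operating characteristic for the interruption rule, so there is no stated figure to reproduce. The check takes each reading of the qualifier in turn.

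**Inputs**

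- Total sample: "A total number of 40 patients with bladder cancer submitted to general anesthesia and open radical cystectomy and urinary diversion will be enrolled", so N = 40. Ten blocks of four also give 10 × 4 = 40.
- Allocation 1:1, so 20 per arm. Only the 20 study-group patients are titrated.
- Trigger: one SAE.
- Per-patient SAE probability p: not in the document. It is assumed and varied, taken as equal and independent across patients.

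**Formula.** P(at least one SAE) = 1 − (1 − p)^n; expected number of patients with an SAE = n × p.

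**Broad reading: the qualifier governs only the last item (n = 40)**

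| Assumed p | P(at least one) | Expected patients |
|---|---|---|
| 1% | 1 − 0.99^40 = 33% | 0.4 |
| 2% | 1 − 0.98^40 = 55% | 0.8 |
| 5% | 1 − 0.95^40 = 87% | 2.0 |
| 10% | 1 − 0.90^40 = 98.5% | 4.0 |

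Solving 1 − (1 − p)^40 = 0.95 gives p = 1 − 0.05^(1/40) = 7.2%. Below that rate an interruption is possible or likely, but not close to certain.

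On this reading a significant prolongation of stay from any cause is an SAE and meets the interruption sentence. The recording and reporting sentence reaches it only if it is also treatment-related. The text would thus interrupt the trial for an event that it does not require to be recorded as an SAE.

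**Narrow reading: the qualifier governs the whole list (n = 20)**

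| Assumed p | P(at least one) | Expected patients |
|---|---|---|
| 1% | 1 − 0.99^20 = 18% | 0.2 |
| 2% | 1 − 0.98^20 = 33% | 0.4 |
| 5% | 1 − 0.95^20 = 64% | 1.0 |

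A 95% chance of interruption would need p = 1 − 0.05^(1/20) = 13.9%.

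On this reading the interruption and reporting sets nearly coincide, but recording becomes lopsided. Suppose, for illustration, that the true rate of serious events is 5% in both arms. The expected count is 20 × 0.05 = 1.0 in each. The SAE record would show at most 1.0 in the study group, fewer if some events are not attributed to titration, and exactly 0 in controls.

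**A concrete case.** A control patient has a pneumothorax after an hourly recruitment maneuver.

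- Under the narrow SAE definition it does not count, because this patient was never titrated.
- The primary pulmonary complication definition does not name pneumothorax. It lists infiltrates or atelectasis, abnormal breath sounds, a low PaO2/FiO2 ratio and ventilatory support. The event might enter through one of its signs, but not as a pneumothorax.
- Table 1 does not name it either.

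The same event in a study-group patient would be recorded if someone attributed it to titration, and anyone but the patient may know the arm when making that judgement.

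**The case against.** The strongest reply is that the narrow reading is the natural one. The AE and SAE definitions are built in parallel, each closing with the same link to titration, and the SAE list opens with barotrauma, a ventilation injury. Any SAE would then already mean a titration-associated one, the restriction to treatment-related events would roughly repeat this, and an ordinary long stay after cystectomy would trigger nothing. This carries weight: the text is ambiguous and not provably contradictory. It does not remove the problem, because the narrow reading is the one that excludes controls from the SAE record.

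It can also be said that little is lost. Table 1 events, length of stay and mortality are endpoints in every patient, and daily visits and calls run to day 28. That stands for a leak, a reoperation or a death, which would be captured as outcome data even if not labelled an SAE. It does not stand for an event that no endpoint names, such as pneumothorax.

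A reader might go further and infer either of two stronger claims.

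- *The trial is almost sure to be halted.* This needs the broad reading and an assumed rate of about 7% or more. The article says only that complication risk is increased, and the SAE item is limited to significant prolongation. An interruption for investigation is also a pause, not termination.
- *The unblinded team alone decides whether to stop.* The article names no decision-maker. It requires an investigation and sends treatment-related SAEs to national and local ethics committees. Who judges causality and who allows a restart are details that an article commonly leaves to the full protocol, so their absence is not held against the plan.

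**Conclusion.** The point holds as a defect in how the rule is stated. The recording and interruption sentences use different event sets, the reach of the titration qualifier is unclear, and each reading has its own fault. On the broad reading an unrelated prolonged stay could interrupt the trial without having to be recorded as an SAE, with a probability that cannot be fixed from the document: 33% to 55% at an assumed 1% to 2%, 87% at 5%. On the narrow reading half the randomized patients, 20 of 40, cannot contribute an SAE, and recording in the other half depends on attribution where only participants are blinded.

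The probabilities rest on assumed, equal and independent rates. The exclusion of controls under the narrow reading rests on no rate, only on the text and on titration being confined to one arm. The consequence is for safety recording and the by-arm safety comparison; no effect on the analysis of the primary endpoints is shown.

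**What to change.** Amend the section *Adverse events and interruption of the trial* as follows.

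1. Record every SAE on the case report form in both arms, whatever its suspected cause, with relatedness as a separate field, and tabulate SAEs by arm both overall and by relatedness.
2. State which items of the SAE list the titration qualifier covers.
3. Have the sponsor reconcile the reporting and interruption sentences around one stated event set. Which set should interrupt the trial is for the sponsor and the ethics committees; this review does not choose it.

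The cost is a short amendment and slightly more recording in 40 patients, with no change to randomization, sample size or endpoints. The article describes the trial as ongoing, so the amendment should also say how events in patients already enrolled are to be handled.
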